### Timelines

Ethical approval was obtained in August 2015. Training of exercise instructors was undertaken in August and September 2014 and July 2015. Recruitment of participants for the study started in September 2015 for the first intervention period (first patient in) and will be continued until March 2016 (last patient in). All participants are expected to have completed the intervention period in July 2016. All participants are expected to have completed the study by February 2018 (last patient out).

### Expert report

The study will be assessed by an independent organization (XCENDA, http://www.xcenda.de/index.php/willkommen.html).

## Discussion

Despite the strong evidence for the short-term effects of physical exercises on symptoms in knee and hip OA [8, 15, 16], many open questions remain with respect to (I) the incorporation of interventions into patient care in a regular health care setting, (II) long-term effects of the intervention as well as its impact on disease progression, (III) dose–response-relationship according to FITT principles (frequency, intensity, type and time of training) and (IV) knowledge on variables that act as confounders for treatment response. Open questions are also related to (V) the economic efficiency of exercise interventions in the treatment of hip and knee OA and to (VI) safety aspects of the intervention [8, 11, 15].

This study proceeds in a real health care setting and has the potential to answer questions in the aforementioned research areas.

(I) This study allows us to determine whether the efficacy of an exercise intervention proofed in a randomized controlled trial can be transferred into effectiveness into a real life situation with less standardized and controlled conditions. The intervention described in this study protocol has been derived from a previously tested exercise intervention in patients with hip OA [17, 20]. Yet some adaptations to the intervention had to be made to give consideration to the needs and organizational framework of the health care provider: the formerly 12-week intervention with one supervised session/week and two additional home-exercise sessions/week was reduced to 8 supervised sessions. Patients are instructed to perform the accompanying home-exercise sessions for at least 11 weeks according to the exercise manual every participant receives [21]. Aside from this change that is related to the frequency and duration of the exercise intervention, the population under consideration has been extended: the RCT was conducted on subjects with hip OA only. As prevalence for knee OA in comparison to hip OA is even higher, the program will be offered to patients with hip and/or knee OA. Subjects with knee OA will therefore substitute some of the hip-exercises with knee-specific exercises. On this note, subjects with knee OA receive an amendment for the exercise manual with knee-specific exercises. Results of this study are therefore very valuable as they allow us to verify whether an “evidence-based exercise intervention” can successfully be implemented into everyday routine or not.

(II) Our follow-up data will be gathered up to 2 years after the initiation of the supervised exercise intervention and will therefore give information on clinical and economic outcomes in the long-term.

(III) The intervention program of this study is predefined and we do not differentiate between different dosages. Nonetheless data on adherence to exercise can be related to effect size and may allow an interpretation on continuity of an exercise intervention in relation to response, whereby confounders for exercise adherence such as pain or dissatisfaction with the intervention etc. have to be considered as well. Another aspect that is related to exercise dosage is the possibility to compare results of this study to other interventions with different exercise frequencies, intensities, times and types of intervention (FITT). This comparison may therefore contribute to the knowledge gained with respect to dose–response relationships of exercise interventions in OA.

(IV) Aside from the comparison of different interventions in general, an individual perspective may gather new knowledge in terms of personal contextual factors that are related to intervention outcome. Identification of possible predictors of treatment responsiveness is therefore another important issue of this research. For example data of previous studies report a gender-specific response to exercise [34, 35]. Additional confounders may be related to baseline pain level, self-efficacy, socio-demographic data etc. In the context of this study, a responder analysis will be conducted according to the OMERACT-OARSI Set of responder criteria [25]. A sub-analysis comparing personal contextual factors of responders versus non-responders may allow a better understanding of relevant prerequisites for successful exercise participation and therefore facilitate individualized treatment recommendations in OA.

(V) Considering published reports on cost-effectiveness of non-pharmacologic, non-surgical interventions for hip and/or knee OA, Pinto and colleagues concluded in their review in 2012 that there is only limited evidence for the cost-effectiveness of conservative treatments for hip and knee OA. In this context they highlighted the need for more high-quality economic evaluations [36]. Since then studies have been published that indicate no cost-saving but cost-effectiveness of exercise interventions in knee or hip OA [37, 38]. In addition, an increasing number of study protocols include economic outcomes and underline the need for the evaluation of economic outcomes aside from clinical measures [39–41]. The aforementioned studies as well as the trial of this protocol will allow a better understanding of cost-utility measures in consideration of different exercise programs and populations under study.

(VI) Although non-pharmaceutical trials are not obligated by law to report on adverse events, safety should be evaluated in clinical trials. Knowledge on adverse events may allow a more precise determination of contra-indications for a given exercise setting and/or population group. Report of adverse events is also important as exercise interventions can initially result in a slight increase in pain [42]. Knowledge on potential short-term side-effects in the primary phase of the intervention period is important as it allows health care providers to inform patients about potential harms with no significant lasting effect on health outcomes. Another important safety aspect is related to frequency and severity of adverse events according to the mode of delivery: Reports on adverse events related to exercises may differ between group sessions and home-based exercises. Safety in the home setting may be hampered as exercises are not controlled by a health care professional and the environment may be less appropriate for the execution of exercises (i.e. tripping hazards are more likely in a home-based setting). Information on adverse events is requested in the self-administered questionnaires at the end of the intervention period. This study may therefore gain knowledge on safety aspects and subsequently allow recommendations to improve safety of supervised as well as independently undertaken exercises. However it has to be mentioned that a reporting bias-especially in the context of home-based exercises - cannot be ruled out, as no immediate adverse event reporting is implemented in this study.

There are further limitations to our study which are—from our perspective—mainly related to concomitant health care interventions, limited long—term follow—up data and the statistical power in terms of economic evaluations.

Referring to the first point it has to be mentioned that all participants of the study are allowed to take part in additional health care offers. This holds true for participants of the control group as well. They may also attend the hip and knee training under study within the follow-up phase. This cannot be prohibited as all insurance holders have the same rights to participate in health care services offered. The exclusive participation in the assigned intervention (supervised exercise versus matched pair control group) can therefore only be guaranteed for the first 3 month of the study. This timeframe is also relevant for the evaluation of the primary outcomes. To control for potential confounders related to additional health care interventions, all follow-up questionnaires ask for participation in any course or training offer.

Although follow-up data for two years will be gathered in the context of this trial, statements on the effect of the intervention in the long run such as time to surgery and disease specific health care costs may be hampered. If 24-months evaluations are positive in terms of study outcomes, a protocol amendment for a 5-year follow up may be considered.

This study has 80 % power for unfavorably high cluster effects, in realty probably more than 90 % power to detect clinical relevant changes in the primary outcomes of the trial. Aside from clinical outcomes, cost-utility measures are of special interest in this study. Yet economic outcomes are expected to have much smaller effect sizes. We therefore decided to include all eligible patients, willing to participate in the trial, to increase power for the economic evaluation.

In due consideration of the burden of OA from an individual as well as economic perspective, the importance to evaluate the effectiveness and cost-efficiency of conservative treatment strategies is obvious. This applies in particular for lifestyle interventions such as physical exercises as they can be carried out by the patient himself and are therefore of special importance in the treatment of chronic diseases such as OA. Results of this trial will document accurately the effects of exercises on clinical and economic outcomes as well as safety aspects in a health care setting on the basis of a large sample size. As such, results of this trial should provide externally valid exercise recommendations in hip or knee osteoarthritis.

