### Outcome measures (Table 4, Fig. 5)

**Table 4 Tab4:** Outcome measures

Characteristics & confounders	Description and instrument	Data source	Sample	Collection points
Patient’s characteristics	Date of birth, gender, ethnicity, BMI (height, weight), site (s) of OA diagnosis, date of first OA diagnosis, labour situation (working, retired, unemployed, in rehabilitation status)	SAQ, IDB	IG, CO	t0, t3, t6, t12, t24
Primary outcome measure	Clinical Outcomes			
Pain	WOMAC Index 3.1 German (11-box NRS): subscale pain	SAQ	IG, CO	t0, t3
Function	WOMAC Index 3.1 German (11-box NRS): subscale physical functioning	SAQ	IG, CO	t0, t3
Secondary outcome measures	Clinical Outcomes		IG, CO	
Stiffness, disease specific impairment	WOMAC Index 3.1 German (11-box NRS): subscale stiffness, overall score	SAQ	IG, CO	t0, t3, t6, t12, t24
Pain, physical function	WOMAC Index 3.1 German (11-box NRS): subscale pain, subscale physical function	SAQ	IG, CO	t6, t12, t24
Health related quality of life	VR-12 incl. VR-6D utility index (4-week-time-slot)	SAQ	IG, CO	t0, t3, t6, t12, t24
General Self-Efficacy	General self-efficacy scale (GSE)	SAQ	IG, CO	t0, t3, t6, t12, t24
Response to exercise	Omeract-OARSI Set of Responder Criteria: composite score with minimum absolute and relative change levels for pain or pain & function	SAQ	IG, CO	t0, t3, t6, t12, t24
Physical activity status	Habitual physical and sports activity status	SAQ	IG, CO	t0, t3, t6, t12, t24
Time to surgery	Endpoint “elective joint replacement”	IDB	IG, CO	t0, t3, t6, t12, t24
	Patient satisfaction			
	Modified version of the ZUF-8 Questionnaire to assess patient satisfaction	SAQ	IG	t3
	Economic data			
Unspecific and specific (OA-related) health care costs	Out-patient costs, hospital costs, costs related to drugs, adjuvants and physical modalities, rehabilitation costs, sick-pay	IDB	IG, CO	tm24, tm18, tm12, tm6 t0, t3, t6, t12, t24
Unspecific/specific (OA related) periods of disability	Days of disability (overall and related to OA)	IDB	IG, CO	tm24, tm18, tm12, tm6 t0, t3, t6, t12, t24
Intervention related costs	Costs for human and physical resources/session	IDB	IG	t3, t6, t12, t24
	Adherence to exercise			
Training adherence	Summarized number of attended training sessions according to training log	SAQ	IG	t3
	Safety evaluation			
Adverse events and side-effects	Summarized number and details of adverse events and side-effects according to training log	SAQ	IG	t3

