Patient satisfaction (IG only, t3) will be quantified by participants of the IG with a four point Likert scale using a modified and shortened version of the ZUF-8 [30, 31]. Modifications were made in order to adapt the eight item instrument to the outpatient setting.Patient characteristicsBody Mass Index (BMI), site (s) of OA joint diagnosis, artificial joint replacement (hip or knee and time of event).Safety evaluation (IG only, t3)Description of adverse events within the previous 11-week intervention period including frequency, intensity and duration of exercise related pain and possible reasons. Participants get a training log for home-based exercises where they are asked to report adherence as well as exercise related adverse events. In this way summarized data can be provided by the participants at the end of the intervention period by reviewing the training logs. Aside from this study-related safety report, patients are urged to contact their personal trainers or physicians in case of adverse events and side-effects.Adherence to exercise (IG only, t3)Number of attended training sessions (group and home-based exercises). In case of omitted sessions: Reasons for non-compliance.Socio-demographic data (insurance data base)The following socio-demographic data will be readout of the data base: date of birth, gender and labor situation (working, retired, unemployed, in rehabilitation status), complexity of work (from 1 = low to 4 = high), level of education (1 = no graduation to 4 = High School), highest level of educational attainment (from 1 = no qualification to 6 = doctoral degree), contractual form (permanent/fixed term contract, full time/part time).Economic data (insurance data base)Patient-specific economic data comprise (1) unspecific and (2) specific osteoarthritis related health care costs for the diagnosis of hip and/or knee OA, (3) Specific and unspecific days of disability and (4) intervention related costs for the exercise program:(1) Unspecific health care costs (overall costs): Sick-pay, hospital costs, out-patient costs, rehabilitation costs and costs related to drugs, physical modalities and adjuvants.(2) Specific diagnosis (hip and knee OA) related health care costs: Sick-pay, hospital costs, out-patient costs, rehabilitation costs and costs related to disease related drugs, physical modalities and adjuvants.(3) Specific (hip and knee OA related) and unspecific days of disability.(4) Intervention related costs include human and physical resources that are required for the institutional exercise sessions. Intervention related costs will be added to the above mentioned diagnosis related costs for all participants of the intervention groups according to the number of their scheduled training session (8 units).

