#### Economic evaluation

Cost-efficiency of the intervention will be quantified on the expanded perspective of the payer. If a dominant strategy doesn’t exist (i.e.: lower costs and higher health related effects in the intervention group), the costs will be related to the effects. The costs (including the supplementary costs of the pilot offer for participants) will be related to the differences between the groups (Double-Difference Method, two years pre and two years post intervention) in Quality Adjusted Life Years (QALYs, equation 1) and health related effects (WOMAC Index: equation 2). The costs of the intervention will further be related to the differences in costs (Double-Difference Method of the health care costs (unspecific health care costs (overall costs), specific health care costs and the costs for days of disability (human capital approach): equation 3). The time to surgery will be estimated using the Kaplan-Meier method. For the economic evaluation all participants have to be members of the insurance the period from 24 months before baseline (tm24) up to 24 month after baseline (t24).

Equation 1: Cost-Utility Analysis (CUA) = Incremental Cost Utility Ratio (ICUR)$$ ICUR\kern0.49em =\kern0.49em \frac{\varDelta\ \mathrm{Cost}}{\varDelta\ \mathrm{QALYs}} $$

Equation 2: Cost-Effectiveness Analysis (CEA) = Incremental Cost-Effectiveness Ratio$$ ICER\kern0.49em =\kern0.49em \frac{\varDelta\ \mathrm{Cost}}{\varDelta\ \mathrm{Effect}} $$

Equation 3: Cost-Benefit Analysis (CBA) = Incremental Cost-Benefit-Ratio$$ ICBR\kern0.49em =\kern0.49em \frac{\varDelta\ \mathrm{Cost}}{\varDelta\ \mathrm{Benefit}} $$

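### Controls may take the study training after month 3, but its cost is charged to the intervention group only, so the as-matched 24-month cost-utility analysis overstates the incremental programme cost

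*Protocol article*

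**What the plan says.** Four parts of the protocol article bear on this.

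- **Access to the training (Discussion, limitations).** Of the controls it is said: "They may also attend the hip and knee training under study within the follow-up phase". The reason given is that all insured persons have equal rights to the insurer's offers. Exclusive participation in the assigned condition "can therefore only be guaranteed for the first 3 month of the study".
- **Costing rule (Outcome measures, economic data).** "Intervention related costs will be added to the above mentioned diagnosis related costs for all participants of the intervention groups", and the amount is set "according to the number of their scheduled training session (8 units" per person. Table 4 has a matching row, described as "Costs for human and physical resources/session", with the intervention group as its only sample and t3, t6, t12 and t24 as collection points.
- **Costs taken for both groups (same section).** The overall health care costs are listed as "Sick-pay, hospital costs, out-patient costs, rehabilitation costs and costs related to drugs, physical modalities and adjuvants". The insurer's own training courses are not named there.
- **Horizon (Economic evaluation).** Costs and effects are compared by a "Double-Difference Method, two years pre and two years post intervention", from the extended perspective of the payer. Table 4 collects the VR-6D utility and the WOMAC in both groups up to t24.

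The article does not exclude, censor or cost a control who takes the course. The Discussion adds that every follow-up questionnaire asks about attendance at courses, but gives control of confounding as the purpose and does not link the answers to costing.

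**The concern.** A comparison of groups as matched may include crossover, provided that each group carries both the effects and the costs of what its members received. The stated rule separates the two. A control who takes the training between t3 and t24 contributes any gain in utility to the control mean, but the eight sessions enter no cost total. The insurer, whose perspective is taken, still bears them.

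The double difference does not remove this. It subtracts costs from before baseline, and the missing item arises after baseline.

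At stake is the numerator of the incremental cost-utility ratio, and of the other two ratios where they carry programme cost. The article describes cost-utility as of particular interest in this study. It also computes ratios only where neither strategy dominates, so an overstated cost difference can affect whether dominance is declared.

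**Working it through.** **Inputs from the article.** 700 participants per group (Sample size). Eight scheduled units per intervention participant (economic data). Crossover is ruled out only for the first 3 months of a 24-month horizon, which leaves 24 − 3 = 21 months in which a control can attend.

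**Inputs not given.** The share *p* of controls who attend, and the programme cost *k* per person for eight units. The article states no figure on this point that could be reproduced. *p* is therefore assumed at 5%, 10% and 20%, and results are in units of *k*. A control who attends is assumed to use the same eight units.

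**Step 1: programme-cost component.**
Rule as written: *k* − 0 = *k*.
Consistent costing: *k* − *pk* = *k*(1 − *p*).
Relative overstatement: 1/(1 − *p*) − 1. Absolute overstatement: *pk* per person.

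| *p* | Consistent component | Overstatement | Uncosted programmes (700*p*) | Uncosted sessions (× 8) |
|---|---|---|---|---|
| 5% | 0.95*k* | 1/0.95 − 1 = 5% | 35 | 280 |
| 10% | 0.90*k* | 1/0.90 − 1 = 11% | 70 | 560 |
| 20% | 0.80*k* | 1/0.80 − 1 = 25% | 140 | 1120 |

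**Step 2: total incremental cost.** Let *dH* be the double difference in all other costs. The rule as written gives *k* + *dH*; consistent costing gives *k*(1 − *p*) + *dH*. The absolute error is still *pk*, but the relative error depends on *dH*:

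| *p* | *dH* = +0.5*k* | *dH* = 0 | *dH* = −0.5*k* |
|---|---|---|---|
| 5% | 1.5/1.45: 3% | 5% | 0.5/0.45: 11% |
| 10% | 1.5/1.40: 7% | 11% | 0.5/0.40: 25% |
| 20% | 1.5/1.30: 15% | 25% | 0.5/0.30: 67% |

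If savings elsewhere lie between (1 − *p*)*k* and *k*, the rule as written shows a net cost where consistent costing shows a saving. At *p* = 10% that is between 0.90*k* and *k*.

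**Step 3: the ratio.** Suppose an attending control gains a fraction *r* of the programme's QALY benefit, and *dH* = 0. Relative to a study without crossover, the ratio is 1/(1 − *pr*) under the rule as written and (1 − *p*)/(1 − *pr*) with consistent costing.

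| *p* | *r* = 1: as written / consistent | *r* = 0.5: as written / consistent |
|---|---|---|
| 5% | 1.05 / 1.00 | 1.03 / 0.97 |
| 10% | 1.11 / 1.00 | 1.05 / 0.95 |
| 20% | 1.25 / 1.00 | 1.11 / 0.89 |

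With *dH* = 0, the rule as written exceeds consistent costing by the factor 1/(1 − *p*) at either *r*. Consistent costing gives the correct as-matched ratio. It returns the no-crossover ratio only if attending controls gain the full benefit.

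**The case against.** **The numerator may be right for another contrast.** If the target is programme against no programme, charging *k* to one group and nothing to the other is correct, and crossover only dilutes the effect. This stands as a reason to name the contrast. It does not rescue the rule: the article describes no adjustment that would remove crossover from the effects, so what it computes is the as-matched contrast, where the controls' cost belongs.

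**A stronger reading is tempting:** that there are two errors, in cost and in effect, both biasing the ratio against the programme. The documents do not support it. The narrower effect difference belongs to an as-matched contrast, and the Discussion discloses the crossover that causes it; it is not a costing error. Step 3 also shows that the correctly costed ratio can fall below the no-crossover value. Nor can 5% to 25% be read as the error in total cost or in the ratio generally, since the share attending, the session cost and the other cost differences are all unknown.

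**Crossover is disclosed and recorded.** True, and this makes the repair easy. But the disclosure treats crossover as a confounder and never connects it to the costing rule.

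**Insurance data might already contain the course.** Table 4 names the insurance data base as the source of programme costs, and the Economic evaluation section includes the offer's additional costs for those taking part without naming a group. This cannot be excluded outright. However, the economic-data paragraph treats programme cost as a separate item to be added, and adds it for the intervention group only.

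**This is detail for a fuller document.** Silence could be left to an economic analysis plan. Here the article states a rule and fixes the sample, and that rule gives the wrong total for attending controls.

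**Conclusion.** The point holds for the economic evaluation. As written, the as-matched analysis keeps the effect of the training in controls who attend after t3 and omits its cost, which overstates the incremental programme cost by *pk* per person. In relative terms the programme-cost component is overstated by 5%, 11% or 25% if 5%, 10% or 20% of controls attend. These shares are assumptions, and if no control attends there is no error. The effect on total incremental cost can be smaller or larger, depending on the other cost differences.

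The conclusion rests on two readings: that the insurer's courses are not already within the cost categories taken for both groups, and that the ratio is meant as the comparison of the groups as matched. Both are the natural readings, but the article confirms neither outright.

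A reader might infer that the primary analysis is compromised too. It is not: the primary outcomes are measured at t3, within the period for which the article guarantees exclusive participation. The change should be made before the economic analysis, but it does not touch the confirmatory result.

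**What to change.** 1. Charge the per-session programme cost to every participant of either group who attends a course up to t24, in the period attended and on the same scheduled-session basis in both groups. This also covers an intervention participant who takes a second course.
2. In Table 4, set the sample for intervention-related costs to both groups, and align the economic-data paragraph with it.
3. State in the Economic evaluation section that the cost-utility ratio is the as-matched contrast including crossover.
4. Report the number of attending controls and when they attended.
5. If an analysis censoring controls at course start is wanted, label it a sensitivity analysis only and warn that the censoring may be informative. Entry to the course needs a physician's referral for hip or knee complaints, so controls who attend may have worse symptoms than those who do not.

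The cost is a little extra costing work. Every follow-up questionnaire already asks about course attendance, and participants register for the courses, so registrations could serve as a check if the data-privacy arrangements allow the link.
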